### Randomization

After completing the baseline assessments, participants will be randomized using MSK’s secure computer system that ensures full allocation concealment. Randomization will be 1:1 (MT:CBT) using randomly permuted blocks of random length, which are stratified by study site, current anxiety medication use (yes or no), and preferred language (English or Spanish). The principal investigator and biostatistician will be blinded to treatment assignments.

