### Analytical Approach

#### General Description

Analyses will be conducted using the intention-to-treat principle (ie, participants will be analyzed according to their randomly assigned treatment group regardless of dropout or treatment adherence status). Given that CBT is widely recognized as a first-line therapy for anxiety, the study team opted to test the noninferiority of MT to CBT, with the goal of understanding whether MT can be an appropriate treatment option for patients who lack CBT access or do not wish to pursue CBT. To provide complementary information for treatment decision-making, the study team will also test which intervention is superior for addressing fatigue and other symptoms co-occurring with anxiety. For all specific aims, the main analytical tool will be a linear mixed-effects model (LMM) because the primary outcome (anxiety) and secondary outcomes (fatigue, depression, insomnia, pain, cognitive dysfunction, and health-related quality of life) are repeated continuous outcomes over time [142]. This statistical procedure takes into account within-subject correlations from repeated measurements in the same subjects and allows the estimation of between-group differences without necessitating the exclusion of participants with missing data. The general template of each LMM will model the outcome as a function of the treatment arm and assessment time (categorical), controlling for the randomization stratification variables (baseline anxiety medication use, preferred language, and study site) and including a subject-specific random intercept. The general LMM template will be tailored to test the specific aim hypotheses by adding interaction terms (eg, time-by-intervention) and additional covariates of interest to the model and by reparametrizing the assessment time variable to focus on specific contrasts.

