#### Aim 1—Hypotheses 1(a) and 1(b)

Outcome measure trajectories will be plotted by randomization arm over time. Each outcome measure will be summarized at each assessment time by treatment arm using descriptive statistics. Comparisons between randomization arms with respect to changes in symptom outcomes will be based on specific coefficients from time-by-arm interactions added to the general LMM template described above in the *General Description* section. Specifically, the model will include all time points (categorical) at which the outcome was assessed (baseline and weeks 4, 8, 16, and 26), and the time-by-arm interaction will include multiple coefficients corresponding to the time-by-arm interaction at each discrete postbaseline time point. However, statistical inferences will focus on the interaction coefficients at 8 and 26 weeks, which are interpreted as the differences between arms in change from baseline to 8 and 26 weeks, respectively. For hypothesis 1(a), the 2 primary end points are HADS anxiety score changes at 8 weeks and 26 weeks. On the basis of the LMM coefficients for the time-by-arm interaction at weeks 8 and 26, 2 tests will be performed to determine whether MT is noninferior to CBT at reducing the HADS anxiety subscale score within a noninferiority margin of 0.35 SD for both comparisons. The noninferiority of MT to CBT will be tested at a significance threshold of *P*<.025 for each comparison, controlling the overall type I error at *P*=.05 for the primary end point comparisons. For hypothesis 1(b), a similar LMM evaluating BFI scores over time will be used to test whether the MT arm had significantly greater improvement in fatigue (BFI score) compared with the CBT arm at weeks 8 and 26. In contrast to the primary end point noninferiority comparisons, these tests will be superiority tests. For other comorbid symptoms (eg, depression and insomnia) and quality of life, the methods described for hypothesis 1(b) will be used to compare the treatment arms. Given that a small number of cancer survivors may experience disease recurrence during the 26-week study, sensitivity analyses will be performed, excluding those individuals who experienced a recurrence during the study period. These sensitivity analyses will not replace the primary analysis.

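### As naturally read, the Aim 1 model enters the stratification factors in a way that has essentially no effect on the week 8 and week 26 noninferiority tests; adding factor-by-time terms is an optional, nearly free improvement

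*Protocol article*

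**What the plan says.** The Randomization section allocates 1:1 in permuted blocks, "stratified by study site, current anxiety medication use (yes or no), and preferred language (English or Spanish". All three factors are fixed at baseline.

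Under General Description, every mixed model starts from a template of arm and categorical time, "controlling for the randomization stratification variables (baseline anxiety medication use, preferred language, and study site) and including a subject-specific random intercept". The template may be tailored by "adding interaction terms (eg, time-by-intervention) and additional covariates of interest to the model".

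The Aim 1 section does that tailoring for the primary hypothesis. Comparisons rest on "specific coefficients from time-by-arm interactions added to the general LMM template described above", and "the model will include all time points (categorical) at which the outcome was assessed (baseline and weeks 4, 8, 16, and 26"). Inference is on the week 8 and week 26 interaction coefficients, "which are interpreted as the differences between arms in change from baseline to 8 and 26 weeks, respectively". No interaction of a stratification factor with time is named. Fatigue gets a similar model, and the other symptoms and quality of life follow the fatigue methods.

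**The concern.** Someone reading the General Description would take the two noninferiority tests to be adjusted for the factors used in randomization. In the model as set out for Aim 1, that adjustment does not reach the tested coefficients. A main effect of a fixed characteristic changes a participant's level at every visit by the same amount, and the tested quantity is a change between visits.

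Precision is at stake. Stratified allocation balances the factors between arms. If they also predict change in HADS anxiety, an analysis that does not let them act on change leaves that predictable variation in the residual. The reported standard error is then somewhat too large and the noninferiority interval somewhat too wide. The same applies to fatigue and the other secondary outcomes.

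**Working it through.** **1. The plan's own power figure.** Inputs from Sample Size and Power: 150 per arm, 15% attrition (127.5 per arm), margin 0.35 SD, one-sided 0.025, two-sample test on change scores. The standard error in SD units is √(2/127.5) = 0.1252, and 0.35/0.1252 = 2.795. Power = Φ(2.795 − 1.96) = 79.8%, so the stated 80% reproduces. It comes from an unadjusted test and does not depend on how the strata enter the model.

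**2. The cancellation.** For participant i at visit j, with factors z_i, arm A_i and random intercept b_i:

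y_ij = μ + βA_i + τ_j + δ_jA_i + γ′z_i + b_i + e_ij

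y_ij − y_i0 = τ_j + δ_jA_i + (e_ij − e_i0)

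Both γ′z_i and b_i drop out. With complete data, δ_j is estimated by the difference in mean change, with variance 2σ_e²(1/n₁ + 1/n₂). Adding z_i as a main effect reduces only the between-person variance, which is not in that expression.

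**3. Complete data, numerically.** With SD 4.2 (from the article), an assumed intraclass correlation (ICC) of 0.5 and 150 per arm, σ_e² = 4.2² × 0.5 = 8.82 and SE = √(2 × 8.82 × 2/150) = 0.4850. In 200 simulated trials per setting (N = 300, stratified 1:1, assumed factor effects), the mean SE was 0.4850 with no factors and 0.4850 with main effects. The estimates agreed to about 1e-12.

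**4. With 15% attrition.** Dropout was assumed to be commoner among medication users. The mean week 26 SE at ICC 0.5 was 0.5129 with and without main effects. Over ICC 0.3 to 0.7 the estimate moved by 0.008 to 0.033 points on average, with a largest single shift of 0.14. The margin is 0.35 × 4.2 = 1.47 points, so the average shift is at most 0.033/1.47 = 2.2% of it.

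**5. What effective adjustment could gain.** Let R² be the share of change-score variance explained by the factors. The article does not give it, so a range is shown.

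- Effective adjustment: power = Φ(2.795/√(1 − R²) − 1.96).
- Main effects only, arms balanced within strata: power = Φ((2.795 − 1.96)/√(1 − R²)).
- True one-sided size with main effects only: 1 − Φ(1.96/√(1 − R²)).

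| R² (assumed) | Effective | Main effects only | Gain (points) | True size |
|---|---|---|---|---|
| 0 | 79.8% | 79.8% | 0 | 2.5% |
| 0.02 | 80.6% | 80.0% | 0.5 to 0.6 | 2.4% |
| 0.05 | 81.8% | 80.4% | 1.4 | 2.2% |
| 0.10 | 83.8% | 81.0% | 2.7 | 1.9% |

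These are change-score approximations to the planned mixed model. In one simulated complete-data trial, the week 8 result was 0.16609 (SE 0.47260) both without strata and with main effects. It was 0.18373 (SE 0.46808) with strata-by-time terms, an SE reduction of 1 − 0.46808/0.47260 = 1.0%.

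**6. What the extra terms cost.** In the attrition simulation at ICC 0.5, the mean week 26 SE went from 0.5129 to 0.5133 (0.5133/0.5129 = 1.0008). Variance components were held at their true values, so this shows the cost of the terms and not any gain. That run crossed three of the four factor contrasts with time.

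**The case against.** The strongest reply is that nothing stated is false. The article nowhere says the factors enter only as main effects. It describes a general template, leaves the list of interactions open, and condenses a fuller protocol. The template also serves Aim 2, where the variable-by-intervention terms use between-person information and the strata terms are not idle. Main effects of stratification factors are a valid choice, and the gain is speculative. If one evenly split binary factor carried R² = 0.05, its two groups would have to differ in HADS change by 4.2 × √(0.05/0.25) = 1.9 points (taking 4.2 as the SD of change), more than the article's 1.7-point MCID. R² = 0.10 would need 2.7 points.

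Most of this stands, and it limits the point. It does not remove it: the Aim 1 section is the tailoring for the primary hypothesis, and it names time-by-arm alone.

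Stronger readings that the article does not support:

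- A reader might infer that the noninferiority tests are invalid or too liberal. Leaving out balanced strata makes the size 2.5% or less, as the table shows.
- A reader might infer that the trial is underpowered. The 80% comes from an unadjusted test and reproduces.
- A reader might say that the control does nothing at all. That is exact only for complete data; with attrition the estimates move slightly.
- A reader might connect the Introduction's remark on groups more likely to drop out of mental health treatment. It concerns race and ethnicity, which are not stratification factors, and leaving treatment is not the same as missing an assessment. The Missing Data section encourages participants who leave treatment to keep completing assessments.

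Simulations that assumed dropout differing by both arm and stratum gave small systematic differences between the two models, about 0.04 to 0.075 points (2.7% to 5.1% of 1.47). The article gives no reason to expect that pattern.

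**Conclusion.** The point holds as an optional improvement and not as a validity error. As naturally read, the stratification terms have no effect on the week 8 and week 26 time-by-arm tests with complete data, and essentially none with the planned 15% attrition. The precision forgone is about 0.5 to 2.7 power points for R² of 0.02 to 0.10, and zero if the factors do not predict change.

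The cancellation is algebra and needs no assumption beyond the main-effects reading. The sizes rest on assumed R², intraclass correlation, factor effects and dropout, none of which the article gives. If the full protocol or analysis plan already crosses the factors with time, the point is met.

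**What to change.** In the Aim 1 model, state that site, anxiety medication use and language each also interact with categorical time, beside the time-by-arm terms. Enter the factors additively and not as crossed strata, since some site-by-language cells may be sparse. Keep the week 8 and week 26 contrasts and the margin as they are. Use the same terms for fatigue and the other secondary outcomes.

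The cost is one sentence and no new data. With three sites there are four factor contrasts (two for site, one each for medication and language). Over four post-baseline visits that makes 4 × 4 = 16 extra fixed effects, negligible with about 255 to 300 participants. FACT-Cog goes only to those who report cognitive difficulties at baseline, so the terms weigh somewhat more there.

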#### Sample Size and Power

The sample size is based on the primary hypothesis that MT is noninferior to CBT for anxiety reduction at weeks 8 and 26. Two tests will be performed to determine whether MT is noninferior to CBT at reducing HADS anxiety at weeks 8 and 26, each with a noninferiority margin of Cohen *d*=0.35 SD for both comparisons. These comparisons will be based on the LMM coefficients for the time-by-arm interaction at weeks 8 and 26; however, the power calculation is based on 2-sample *t* tests of differences between the arms in their change scores. Therefore, the power estimate is conservative, that is, in the LMM-based analysis, there will be slightly higher power than the power calculation presented below, with all other assumptions held constant. Assuming 150 participants are randomized to each arm, 15% attrition, and a 1-sided significance threshold of *P*=.025 (controlling the overall type I error at 0.05 for our 2 primary end point comparisons), there will be 80% power to find MT noninferior to CBT with respect to the HADS anxiety subscale scores at weeks 8 and 26 within a noninferiority margin of Cohen *d*=0.35 SD.

The noninferiority margin was informed by a large study that used multiple rigorous methods to empirically estimate a difference of 1.7 points as the MCID for the HADS scales [120]. In preliminary data from CBT recipients with baseline HADS anxiety subscale scores ≥8, the SD for the HADS anxiety subscale score was 4.2 at week 8 [110]. In addition, in a large acupuncture trial of cancer survivors, among 159 patients with baseline HADS anxiety subscale scores ≥8, the HADS anxiety subscale score SD was 4.0 during follow-up [155,156]. On the basis of these studies, it is assumed that the HADS anxiety subscale score SD will be approximately 4.2. Dividing the raw-score MCID of 1.7 points by 4.2 yields a standardized difference, that is, Cohen *d*=0.40. The noninferiority margin of Cohen *d*=0.35 SD is smaller than the standardized MCID (Cohen *d*=0.40) of the HADS anxiety subscale; as such, the noninferiority margin and statistical approach will find MT to be noninferior to CBT only if MT is not meaningfully worse than CBT.

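### The stated random-intercept covariance is restrictive for five visits over 26 weeks and can understate the week 26 standard error if correlation falls with lag

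*Protocol article*

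**What the plan says.** Under General Description, the protocol article sets one mixed-model template for all aims: arm and categorical time as fixed effects, "controlling for the randomization stratification variables (baseline anxiety medication use, preferred language, and study site) and including a subject-specific random intercept". It then says how the template is adapted to each hypothesis: "by adding interaction terms (eg, time-by-intervention) and additional covariates of interest to the model and by reparametrizing the assessment time variable". These adaptations concern the fixed effects and the coding of time. None touches the covariance.

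The section on hypotheses 1(a) and 1(b) applies the template to the primary outcome: "the model will include all time points (categorical) at which the outcome was assessed (baseline and weeks 4, 8, 16, and 26"). From that fit, "statistical inferences will focus on the interaction coefficients at 8 and 26 weeks", each read as the arm difference in change from baseline. Sample Size and Power gives each test "a 1-sided significance threshold of *P*=.025 (controlling the overall type I error at 0.05 for our 2 primary end point comparisons") and sets the margin: "each with a noninferiority margin of Cohen *d*=0.35 SD for both comparisons".

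No random slope, residual covariance structure or robust standard error is mentioned in these sections or under Missing Data.

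**The concern.** A subject random intercept with independent, constant-variance residuals is compound symmetry: equal variances at all visits and equal correlations between all pairs of visits. The model pools these quantities over the five visits and applies the result to every change from baseline.

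Two features of the design make that doubtful. Visits are between 4 and 26 weeks after baseline, so correlation may well fall with lag, and baseline to week 26 is the longest lag of all. Also, the entry rule truncates the baseline score but not the follow-up scores, so the baseline SD is likely to be smaller.

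The primary decision sets a confidence limit against a margin. If the week 26 standard error is too small, noninferiority to a comparator that the article calls a first-line therapy is declared more often than the nominal level allows. If a standard error is too large, power is lost.

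**Working it through.** **The plan's own figure.** Inputs are in Sample Size and Power: "Assuming 150 participants are randomized to each arm, 15% attrition", one-sided 0.025, margin 0.35 SD. Completers per arm: 150 × 0.85 = 127.5. Power = Φ(0.35 × √(127.5/2) − 1.96) = Φ(0.834) = 0.798, which reproduces the stated 80%. It rests on two-sample t tests of change scores, so it does not involve the mixed-model covariance.

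**Formulas (complete data).**
- Change variance used by the random-intercept model: 2 × (mean variance − mean covariance), averaged over the five visits.
- True change variance at visit t: var(0) + var(t) − 2 cov(0,t).
- Ratio of model SE to true SE = √(model variance / true variance).
- Actual one-sided error = 1 − Φ(1.96 × ratio).

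**Inputs.** The follow-up SD of 4.2 is from the article. All correlations, the baseline SD and any week 4 SD other than 4.2 are assumptions.

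**Decay example.** Correlation 0.75 per visit step, all SDs 4.2 (variance 17.64). Mean correlation = (4×0.75 + 3×0.5625 + 2×0.4219 + 0.3164)/10 = 0.585. Model variance = 2 × 17.64 × (1 − 0.585) = 14.65. True week 26 variance = 2 × 17.64 × (1 − 0.316) = 24.12. Ratio = √(14.65/24.12) = 0.78, error 0.063.

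**Truncation example.** Equal correlation 0.6, baseline SD 2.9, other SDs 4.2. Mean variance = (8.41 + 4×17.64)/5 = 15.79. Mean covariance = (4×7.308 + 6×10.584)/10 = 9.27. Model variance = 2 × (15.79 − 9.27) = 13.04. True variance = 8.41 + 17.64 − 2×7.308 = 11.43. Ratio = √(13.04/11.43) = 1.07, error 0.018 at both weeks.

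**Range of settings** (SE ratio, one-sided error):

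| Assumed correlation | SDs | Week 8 | Week 26 |
|---|---|---|---|
| Equal, 0.6 | all 4.2 | 1.00, 0.025 | 1.00, 0.025 |
| Equal, 0.6 | baseline 2.9 | 1.07, 0.018 | 1.07, 0.018 |
| Linear 0.60 to 0.50 over lags of 4 to 26 weeks | baseline 2.9 | 1.10, 0.016 | 1.01, 0.023 |
| Linear 0.65 to 0.55 | baseline 2.9 | 1.09, 0.016 | 1.00, 0.025 |
| Linear 0.70 to 0.50 | baseline 2.9 | 1.12, 0.014 | 0.95, 0.032 |
| 0.40 + 0.45 × 0.8^(lag/4 weeks) | baseline 3.2, week 4 3.8 | 1.11, 0.015 | 0.90, 0.039 |
| Same | all 4.2 | 1.08, 0.017 | 0.86, 0.047 |
| 0.75 per visit step | baseline 2.9 | 1.03, 0.021 | 0.85, 0.048 |
| Same | all 4.2 | 0.97, 0.028 | 0.78, 0.063 |
| 0.90 per 4 weeks | all 4.2 | 1.20, 0.009 | 0.74, 0.073 |
| 0.95 per 4 weeks | all 4.2 | 1.23, 0.008 | 0.72, 0.078 |
| Baseline with follow-up 0.40, follow-up visits 0.70 | baseline 2.8, week 4 3.8 | 0.88, 0.043 | 0.88, 0.043 |

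SDs not listed are 4.2.

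**Simulation with dropout.** REML random-intercept fits were simulated with 150 per arm, dropout reaching 15% by week 26, the true difference at the margin and 1,500 replicates per setting. The Monte Carlo SE is about √(0.025×0.975/1500) = 0.004. Week 26 error was 0.044 to 0.053 for the two settings with the 0.40 + 0.45 × 0.8^(lag/4) correlation. It was 0.072 for 0.75 per visit with equal SDs. Week 8 error was 0.008 to 0.023 and 0.027 for the same settings. Under true compound symmetry the errors were 0.021 (week 8) and 0.029 (week 26). This agrees with the formulas.

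**The case against.** The best defence is that the article describes a general template and does not say that the random intercept is its only covariance feature. Residual structure, estimation method and robust errors are often left to an analysis plan, which is not shown here. This stands in part: the compound-symmetry reading depends on conventional residuals. But the random intercept is a stated choice, and the listed adaptations leave it alone, so a different structure would depart from the published template.

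A reader might go further and infer any of the following, none of which the article supports:

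- **That the standard errors are wrong at both weeks, or usually too small at week 26.** The article gives no between-visit correlation and no baseline SD. Under equal correlations and SDs there is no error. With mild decay and a smaller baseline SD the two effects roughly cancel at week 26 (0.023 to 0.025).
- **That the entry rule inflates the error.** It casts doubt on equal variances but works the other way. With equal correlations of 0.5 to 0.7 and a baseline SD of 2.5 to 3.2, the error is 0.016 to 0.020 at both weeks. Inflation comes from decay, or from baseline being less correlated with follow-up than follow-up visits are with each other. The largest week 26 figures also assume equal SDs: at 0.75 per visit step, a baseline SD of 2.9 lowers 0.063 to 0.048.
- **That week 8 is harmed in a known direction.** The SE ratio there runs from 0.88 to 1.23.
- **That the sample size or power is misstated.** Both reproduce, and neither depends on this choice.

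**Conclusion.** The point holds as a restrictive modelling choice with a better and nearly free alternative, not as a demonstrated error. Read conventionally, the stated structure gives the week 26 contrast a pooled standard error that ignores its being the longest lag. Under clear decay the one-sided error at week 26 is about 0.03 to 0.08 against 0.025. Under mild decay with a smaller baseline SD it is about nominal. At week 8 it lies between about 0.008 and 0.04, so the test may be conservative or liberal. These figures depend on assumed correlations and SDs and on independent, constant-variance residuals with model-based standard errors. It is worth settling before the data are analysed, because week 26 is one of two primary end points and the split of alpha presumes that each test holds its level.

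**What to change.** For the primary HADS anxiety model, replace the random intercept with an unstructured within-subject covariance across the five visits, fitted by REML with Kenward-Roger degrees of freedom. Name in advance a simpler heterogeneous structure (for example heterogeneous Toeplitz) in case it does not converge. Alternatively, keep the random intercept and base the tests on cluster-robust standard errors. If an unshown analysis plan already does either, the template should say so.

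An unstructured matrix has 5 × 6 / 2 = 15 parameters, which 300 participants support easily, and it contains compound symmetry as a special case. Each change variance is then estimated from its own visits, so the error returns to about 0.025 at both weeks. Use the same approach for the secondary models where the sample allows. FACT-Cog goes only to participants who report cognitive difficulty at baseline, so its model may need the simpler structure.

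The cost is a sentence or two of specification. The week 26 interval may become slightly wider. The planned sample size does not change.
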